#### Preliminary effectiveness

The preliminary effectiveness outcomes are comprised of quality of life, utilization of health services, sustained use intention, and rate of adherence.

Quality of life will be evaluated using the Hong Kong version of the 5-level EuroQol 5-dimension scale (EQ-5D-5L), a validated descriptive system that has been used extensively in different jurisdictions. It consists of five dimensions: mobility, self-care, usual activities, pain or discomfort, and anxiety or depression. Each dimension has five levels of severity, namely, no problem, slight problem, moderate problem, severe problem, and extreme problem [27,28].

Utilization of health services will be measured by the number of attendances at a general practitioner’s office, emergency department, hospital, and general out-patient clinic. The data will be self-reported by subjects with confirmation via medical and attendance certificates [23].

The subjective primary outcome, sustained use intention, will be measured using a three-item, 5-point Likert scale measurement tool [29,30]. The scale ranges from 1 = strongly agree to 5 = strongly disagree. Lower scores indicate a higher chance of using the WMD sustainably.

The objective primary outcome, rate of adherence, will be evaluated by examining the number of days and the average length of time per day that the subject has worn the device. The data will be logged automatically into the system when the subject starts wearing the device.

Background demographics such as age, gender, marital status, educational level, primary caregiver, frequency of caretaking support, experience of using wearable monitoring devices, and eHealth literacy, will be collected at the baseline to account for differences between the groups.

### Data collection

The collection of data will occur at four time-points: baseline (T0), 1 month (T1), 3 months (T2), and 6 months (T3). T2 represents the immediate post-intervention period while T3 represents three months after the intervention for assessing the sustained effect of the program. At T0, baseline demographic data will be collected. Quantitative data will be collected at all four time-points through phone calls by the research assistant. Qualitative data will be collected at T2 through a semi-structured interview.

### Data analysis

Statistical tests will be performed using the software, Statistical Package for Social Sciences (SPSS) version 26. Descriptive analyses will be used to present the baseline demographic data. The differences and changes in outcomes for the quantitative data will be estimated using the Generalized Estimating Equation (GEE). For each outcome, (1) the between the intervention and control group (between-group) effects, (2) the within-group (time) effects, and (3) the group-by-time interaction (group X time) effects will be investigated. However, it is important to note that the validity of the GEE analysis relies on the assumption that data are missing completely at random (MCAR) [31]. Therefore, we will employ Little’s test to assess whether the missing data in our dataset are MCAR. If the test results are significant or indicate non-MCAR data, we will utilize Weighted Generalized Estimating Equation (WGEE) to analyze the outcome measures instead. Intention-to-treat will be our primary choice to analyze the data [32]. The level of significance will be set at p < .05 for a two-tailed test.

The qualitative data from the semi-structured interviews will be examined using the principles of deductive thematic analysis [33]. All focus group interviews will be conducted with audio recordings. Transcription and translation will be performed manually by research team members. To enhance conformability, an audit trail will be maintained to resolve any differences through agreement.

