### Study setting, subjects, and recruitment strategies

The recruitment will be carried out in five community centers. Members of the community centers who have shown an interest in this program will be screened and recruited. The inclusion criteria are: (1) 60 years old or older, (2) owning a smartphone, (3) able to communicate in Cantonese or Mandarin, and (4) able to access the internet. The exclusion criteria are: (1) having a medically diagnosed cognitive impairment, (2) being bedbound, (3) already own a WMD, and (4) involved in other WMD-related studies.

A research assistant will explain details of the study to the eligible subjects. The written consent of the participants and their baseline data will be collected at the community centers. The participants will be randomly assigned to either the intervention or control group using group assignments generated by the Research Randomizer software. The group assignments will be sealed and opened sequentially by the principal investigator at the time of randomization. To maximize the level of double-blinding, participants will be informed that the intervention aimed to promote the use of the WMDs but will not be informed about their specific assignment to the intervention or control group. Furthermore, the research assistant responsible for data collection will remain blinded to the group allocation, while the providers, including community center staff, will not be blinded.

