### Sample size

A power analysis was used to calculate the sample size for this study. We adopted usability as our primary outcome measure. To determine the effect size for our study, we referred to the Overall Acceptability Score [34], where the intervention group scored 45.2 (2.9) and the control group scored 40.4 (1.3). To account for potential differences in our local sample, which may consist of older individuals with lower mobile device literacy, we used a conservative approach and discounted the effect size by one-third for sample size calculation (which was 0.72). This was done to ensure an adequate sample size.

Assuming an alpha value of 0.05, a power of 80%, and an effect size of 0.72 [33], the sample size for each group should be 32. Accounting for a 10% drop-out rate, the total sample size in this study will be 70 (i.e., 35 per group).

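### Baseline factors are collected to account for group differences, but the analysis section states no adjustment; a small covariate set should be fixed in advance, above all for wear-time adherence

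*Protocol article*

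**What the plan says.** Three parts of the Protocol article bear on this point.

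- **Outcome measures, Preliminary effectiveness.** A list of background variables, among them age, educational level, experience with wearables and "eHealth literacy, will be collected at the baseline to account for differences between the groups". The objective primary outcome, rate of adherence, is defined as "the number of days and the average length of time per day that the subject has worn the device", and "The data will be logged automatically into the system when the subject starts wearing the device".
- **Data analysis.** The stated use of the background data is "Descriptive analyses will be used to present the baseline demographic data". For each outcome the GEE is to examine "the between the intervention and control group (between-group) effects, (2) the within-group (time) effects, and (3) the group-by-time interaction (group X time) effects". If the missing data are not completely at random, a weighted GEE (WGEE) replaces it. No covariate is named for either model.
- **Study setting, subjects, and recruitment strategies.** People who "already own a WMD" are excluded. Allocation is by individual randomisation, and no stratification is described.

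**The concern.** The outcome section announces a purpose for the background data that the analysis section does not carry out. Two readings are open, and neither is well fixed.

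1. **No adjustment.** Variation that the collected factors could explain stays in the error term, and any chance imbalance in a prognostic factor passes into the estimated program effect.
2. **Adjustment for factors found to differ.** The covariate set would then be chosen after seeing the data, so the model is not fixed in advance.

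Wear time is the sharpest case. Sustained use intention and EQ-5D-5L can have a baseline measurement that absorbs between-person variation. Wear time cannot: logging begins only once the trial's device is worn, and current owners are excluded. For this outcome the background factors are the main baseline information available.

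**Working it through.** **Inputs from the article.** Two-sided alpha 0.05, power 80%, d = 0.72, 32 per group before dropout, 35 per group randomised (Sample size; Data analysis). The 0.72 was set for usability.

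**Inputs assumed.** R, the multiple correlation of the chosen covariates with the outcome. The article gives no value, so a range of 0 to 0.5 is shown.

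**Step 1. Reproduce the planned figure.** Normal approximation: 2 × (1.960 + 0.842)² / 0.72² = 30.3, so 31 per group. The two-sample t-test gives 31.27, so 32 per group, as stated. This point does not affect that figure.

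**Step 2. Is an unadjusted analysis valid?** In simulated two-group comparisons with 32 per group and 20,000 replicates, at covariate-outcome correlations of 0.3, 0.5 and 0.7, the unadjusted test had a type I error of 4.7% to 5.0%. Its mean estimate was 0.72 for a true 0.72. It is therefore valid and unbiased on average. What is at stake is precision, and the estimate in the one trial that is run.

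**Step 3. Chance imbalance.** The standard error of a standardised baseline difference with 35 per group is √(2/35) = 0.239. Then 0.3/0.239 = 1.255, and the two-sided probability of a difference above 0.3 SD is about 21% for any one covariate.

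**Step 4. What such an imbalance does.** The unadjusted estimate shifts by correlation × imbalance. For a 0.3 SD imbalance:

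| Correlation with outcome | Shift (SD) | Shift / 0.72 |
|---|---|---|
| 0.2 | 0.06 | 8% |
| 0.3 | 0.09 | 12.5% |
| 0.5 | 0.15 | 21% |

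The 21% in the last row is unrelated to the 21% in Step 3.

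**Step 5. Illustrative power.** Adjustment reduces the residual SD by √(1 − R²), so the standardised effect becomes 0.72/√(1 − R²). Two-sample t-test, 32 per group:

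| R | Variance removed (R²) | Power |
|---|---|---|
| 0 | 0% | 80.9% |
| 0.2 | 4% | 82.5% |
| 0.3 | 9% | 84.4% |
| 0.4 | 16% | 87.1% |
| 0.5 | 25% | 90.6% |

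These figures compare two groups at one time, not in a repeated-measures GEE, and they ignore the few degrees of freedom that the covariates use.

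**The case against.** The strongest reply is that the analysis section lists effects to be investigated, not a closed model formula. Nothing in it says unadjusted, and presenting baseline data descriptively does not prevent their use as covariates. A reader might infer that wear time is definitely analysed with three terms and nothing else; the text does not support that. The supportable statement is that no adjustment is stated. It is also fair that a condensed article may leave the covariate list to the full protocol or analysis plan. What survives is narrower: this article announces a purpose for the data, and the analysis it then describes does not serve it.

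Three further inferences should be resisted.

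- **That an unadjusted result would be biased or invalid.** Step 2 shows otherwise, and the standard error already allows for chance imbalance.
- **That the protocol itself treats literacy as a predictor of wear time.** The Sample size section shrinks a borrowed effect because of the local sample, "which may consist of older individuals with lower mobile device literacy". That concerns how far a usability effect carries over to another population. It does not say that literacy predicts wear time, and mobile device literacy is not the eHealth literacy collected at baseline.
- **That prior wearable experience is nearly constant.** Current owners are excluded, but past users are not.

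The objection that 0.72 belongs to usability and that R is assumed also stands. The power table shows how a gain would scale; it is not a forecast for adherence. Finally, no passage says that covariates will be selected by observed imbalance. That is one possible reading of the stated purpose.

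**Conclusion.** The point holds as a mismatch within the article and as a cheap improvement, not as an error that invalidates the analysis. The stated purpose of the background factors has no counterpart in the Data analysis section. On either reading, a small fixed covariate set is better than what is written, most clearly for wear time.

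The one size that rests on the plan's own numbers is the 21% chance, per covariate, of an imbalance above 0.3 SD with 35 per group. The power gain is conditional: about 1.6 points at R = 0.2, 3.5 at 0.3 and 10 at 0.5, using an effect size set for another outcome. If the factors are only weakly prognostic for wear time, the gain is close to nil.

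**What to change.** In Data analysis, state that:

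- the GEE or WGEE for rate of adherence and the other effectiveness outcomes includes a small set of baseline covariates, fixed before unblinding and kept whatever their observed balance, for example eHealth literacy and age (both continuous) and educational level coded in few categories;
- the adjusted group difference is the main result and the unadjusted one is a sensitivity analysis;
- no covariate is added or dropped because of baseline significance tests or observed imbalance.

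Decide in advance whether prior wearable experience belongs in the set.

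The cost is a few lines of wording and a few degrees of freedom, more if education keeps many categories. The variables are already collected.

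### For outcomes with a T0 value, the planned GEE group effect includes a pre-treatment visit and each interaction contrast against T0 is a change score; a T0-adjusted post-baseline contrast is the better estimate of the treatment effect

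*Protocol article*

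**What the plan says.** The protocol's Data analysis section sets out three effects to be examined by GEE: "For each outcome, (1) the between the intervention and control group (between-group) effects", the effect of time, and the group-by-time interaction. It does not say which of these is the treatment effect, at which visit it is read, or how the T0 value of an outcome enters the model. The section also states "The level of significance will be set at p < .05 for a two-tailed test".

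The Data collection section says "Quantitative data will be collected at all four time-points through phone calls by the research assistant", the four being T0, 1 month, 3 months and 6 months.

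On background variables, the section on preliminary effectiveness says that they "will be collected at the baseline to account for differences between the groups". These are demographics and eHealth literacy, not the baseline value of the outcome.

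The Sample size section is a two-group comparison for usability: "Assuming an alpha value of 0.05, a power of 80%, and an effect size of 0.72", from which "the sample size for each group should be 32". It names no visit, no between-visit correlation and no repeated-measures term.

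**The concern.** Read together, the Data collection and Data analysis sections make T0 a level of the repeated outcome. Neither planned group term is then the post-treatment difference between arms.

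- **Group effect.** As an overall (marginal-mean) effect it is an average over four visits, one of them before treatment. As a coefficient in an interaction model with T0 as reference, it is the T0 difference alone, which under randomisation is chance. The protocol does not say which is meant.
- **Group-by-time effect.** With complete data, each contrast against T0 is the difference between arms in change from T0. This is unbiased, but it carries the full noise of the T0 measurement.

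At stake are an estimate that is a quarter too small if the overall group effect is read as the treatment effect, and a power that may differ from the one in the Sample size section, in a direction that depends on an unstated correlation.

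**Working it through.** **Inputs from the protocol.** Two-sided alpha 0.05, power 80%, standardised effect 0.72 (taken as stated), 32 per group before drop-out, 35 per group enrolled, 10% drop-out, visits at T0 and 1, 3 and 6 months.

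**Assumptions, not in the protocol.** The same correlation rho between any two visits (range shown), equal variance at each visit, a constant effect of 0.72 SD at T1 to T3, and zero expected difference at T0. Completers per arm: 35 × 0.9 = 31.5.

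**The plan's own figure.** A two-sample t-test at d = 0.72 gives 80.9% power with 32 per group and 79.6% with 31, so 32 per group is reproduced. With 31.5 per group a single-visit comparison has 80.3%.

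**Size of the diluted group effect.** (0 + 0.72 + 0.72 + 0.72)/4 = 0.72 × 3/4 = 0.54, which is 25% below 0.72. This does not depend on rho.

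**Standardised effects for power.**
- Change from T0 at one visit: 0.72/√(2(1−rho)).
- Average over T0 to T3: 0.54/√((1+3rho)/4).
- One visit adjusted for T0: 0.72/√(1−rho²).

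The variance ratio of adjusted to change is (1−rho²)/(2(1−rho)) = (1+rho)/2, which is below 1 for every rho below 1.

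**Power, two-sample t-test, 31.5 per arm.**

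| rho | Change from T0, one visit | Average T0–T3 | T0-adjusted, one visit |
|---|---|---|---|
| 0.3 | 66% | 86% | 84% |
| 0.4 | 73% | 81% | 87% |
| 0.5 | 80% | 76% | 90% |
| 0.7 | 95% | 67% | 98% |

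The change score drops below 80% for rho under about 0.5, and the four-visit average drops below 80% for rho above about 0.42. The T0-adjusted single-visit contrast starts at 80.3% when rho is 0 and rises from there.

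**Where the four-visit average is the stronger test.** The squared standardised effects, divided by 0.72², are 2.25/(1+3rho) for the average and 1/(1−rho²) for the adjusted visit. They are equal at rho = 1/3 (2.25/2 = 1.125 and 1/(8/9) = 1.125). Below that, under a constant effect, the diluted average has more power than one adjusted visit, because averaging reduces variance as well as the effect.

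**Like for like.** The T0-adjusted mean of T1 to T3 has about 99% power or more under the same assumptions, so the gain from averaging does not require T0 in the average.

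**Limits of adjustment.** If the true effect at the tested visit is 0.5, the T0-adjusted test with 32 per group (normal approximation) has 52% power at rho 0, 55% at 0.3, 64% at 0.5 and 80% at 0.7.

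**The case against.** The case for leaving the plan alone is a fair one. Group, time and group-by-time in a GEE is a common and valid specification, and the interaction is unbiased under randomisation. The article condenses a fuller protocol, so the coding of the group effect and the handling of T0 may be settled elsewhere. Effectiveness is described as preliminary. Below rho = 1/3 and under a constant effect, the planned overall group test is more powerful than a single T0-adjusted visit, so there is no general loss of power. All of this stands, and it limits the point to the estimate and to the choice of contrast. It does not remove the point: the effects to be tested are stated, and a faithful analysis plan would inherit a group effect that is not the post-treatment difference.

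Reach is also limited. People who already own a device are excluded and the schedule figure is not shown, so whether the technology-acceptance scale or sustained use intention is asked at T0 is not certain. The Data collection wording suggests that it is. Adherence is logged only once the device is worn and has no T0 value.

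A reader might go further and infer that the model contains nothing but group, time and their product. The documents do not say so. They list effects to be investigated, not a full set of covariates, and the reason given for collecting background variables points towards some adjustment.

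**Conclusion.** The point holds for outcomes with a T0 value: EQ-5D-5L, and the technology-acceptance scale or sustained use intention if asked at T0. It rests on T0 being among the repeated outcomes, which is the plain reading but is not stated outright.

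Two parts hold whatever the correlation. An overall group effect that includes T0 understates a constant post-treatment effect by 25% (0.54 for 0.72), or is merely the baseline difference if reference-coded to T0. And the interaction contrast against T0 has larger variance than the T0-adjusted contrast, with adjusted over change equal to (1+rho)/2.

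The effect on power is conditional on rho. The two planned terms fall short at opposite ends of its range, so neither can be relied on for the 80% in the Sample size section. That 80% was calculated for usability only.

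A reader might infer that adjusting for T0 guarantees 80% power. The documents do not support that. Adjustment gives about the planned power or more only for the same assumed effect of 0.72 at the tested visit and the same number of completers, and it does not protect against a smaller or fading effect. Nor do the documents settle that the 6-month visit alone should decide, or which background variables should be covariates; those are choices with trade-offs.

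**What to change.** For outcomes with a T0 value, enter T0 as a covariate (or constrain both arms to a common T0 mean) and model T1 to T3. Define the treatment effect as the T0-adjusted between-arm contrast after baseline. The sponsor should state in advance whether that contrast is read at one named visit or as the T1–T3 average. A single visit three months after the programme answers the question of sustained use but is exposed to fading, while the average is more precise if the effect is steady and blurs one that is not. State that no group effect that includes T0 will be interpreted as a treatment effect. Leave adherence as a comparison of post-randomisation values.

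The cost is a change of wording and one degree of freedom. It needs no further participants or data beyond the T0 values already planned.

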Despite the benefits, recent reports have found that older adults have difficulty maintaining the long-term use of WMD. A study investigating the attitudes of older adults towards WMD has shown that 60% of participants stopped using the device after two weeks [12]. Another study aimed at investigating the effectiveness of WMD on the frequency of physical exercise showed that more than 20% of the older participants stopped using the WMD during the 12-week intervention period and another 50% discontinued the use of device 6 weeks after the intervention [13]. In fact, barriers such as the absence of clear instructions, knowledge, and support on handling the device, and a lack of motivation in learning new things have prevented older adults from continuing the use of WMDs [14].

Community Health Workers (CHW) have been recognized as paid workers who can motivate and support older adults in adhering to health-promoting and self-management activities. A qualitative study revealed that CHWs played a crucial role in facilitating the monitoring of vital signs, promoting physical exercise, and providing health education on older adults with chronic diseases [15]. In fact, CHWs do not necessarily have a professional medical or psychosocial background but do have commonalities with the person they are providing care to, such as age, socioeconomic background, and living place, which allow them to easily build strong rapport and connection with the care recipient [16]. In one study, older adults commented that they felt a sense of understanding, caring, and companionship from their CHW. They were more resilient to set-backs and more motivated to learn because their CHW was able to provide nonjudgmental support [17]. Previous studies discovered that a CHW-led program not only has significant effects on improving health outcomes for older adults [18], but is also cost-effective [19].

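### With 70 subjects and about 7 drop-outs, a non-significant Little's test does not justify assuming MCAR and should not decide whether GEE stays unweighted

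*Protocol article*

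**What the plan says.** The Data analysis section of the protocol article names the main method: "The differences and changes in outcomes for the quantitative data will be estimated using the Generalized Estimating Equation (GEE". It adds that "the validity of the GEE analysis relies on the assumption that data are missing completely at random (MCAR", and sets up a check: "we will employ Little’s test to assess whether the missing data in our dataset are MCAR". The consequence follows: "If the test results are significant or indicate non-MCAR data, we will utilize Weighted Generalized Estimating Equation (WGEE) to analyze the outcome measures instead". No other criterion for switching is given, so a non-significant result leaves unweighted GEE in place. The section gives one significance level, "The level of significance will be set at p < .05 for a two-tailed test", and none specifically for Little's test. It does not state the GEE working correlation.

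The Sample size section fixes the scale. Its calculation, "Assuming an alpha value of 0.05, a power of 80%, and an effect size of 0.72 [33], the sample size for each group should be", gives 32; it then allows for losses: "Accounting for a 10% drop-out rate, the total sample size in this study will be 70 (i.e., 35 per group". The Data collection section sets four time-points: baseline (T0) and months 1, 3 and 6 (T1 to T3).

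**The concern.** A test that fails to reject MCAR has not shown MCAR, least of all when few subjects are incomplete. By the plan's own premise the default analysis needs MCAR, and the only safeguard is a test with limited power at this size. The test result, rather than the design, then chooses the estimator.

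MCAR is also open to doubt here. The intervention arm gets a home visit and fortnightly calls from community health workers, while the control arm uses the device alone (Intervention group and Control group sections). Drop-out could therefore depend on earlier scores and do so differently by arm. If controls with poor scores leave, the remaining controls look better than they should and the group difference is understated.

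**Working it through.** **Inputs from the article.** 35 per arm, four visits, 10% drop-out, effect size 0.72, two-sided 0.05 (assumed to apply to Little's test too).

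**Assumptions not in the article.** Normal outcome with higher scores better; within-subject correlation 0.5; group effect of 0, 0.36, 0.72 and 0.72 SD at T0 to T3; monotone drop-out; Little's test run on the four visit values; drop-out odds ratio of 1.5, 2 or 3 per SD of worse score.

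**Step 1: the plan's sample size.** The normal approximation is n = 2(1.96 + 0.84)²/0.72² = 30.3, so 31 per group. The two-sample t-test gives power of 79.6% at 31 and 80.9% at 32, so 32 is reproduced. 32/0.9 = 35.6 and 31/0.9 = 34.4, so 35 per group is within rounding.

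**Step 2: what the test has to work with.** 70 × 0.10 = 7 drop-outs. Monotone drop-out gives three incomplete patterns (last seen at T0, T1 or T2), so about 7/3 = 2.3 subjects each. Little's statistic sums, over patterns, n × (pattern mean − fitted mean)′ × inverse covariance × (pattern mean − fitted mean). Its degrees of freedom are the observed visits summed over patterns minus the number of visits: (1 + 2 + 3 + 4) − 4 = 6. That is six degrees of freedom informed by about seven incomplete subjects.

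**Step 3: how often the test is significant** (600 trials per setting; each cell gives odds ratios 1.5 / 2 / 3). With truly MCAR data at 10 to 30% drop-out it was significant in 4 to 5% of trials.

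| Drop-out by T3 | Previous score, both arms | Previous score, control arm only | Current, unseen score |
|---|---|---|---|
| 10% | 10 / 20 / 52% | 8 / 12 / 21% | 5 / 9 / 15% |
| 20% | 12 / 40 / 75% | 8 / 15 / 29% | 7 / 12 / 26% |
| 30% | 19 / 55 / 91% | 8 / 15 / 37% | 9 / 14 / 35% |

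At the planned 10%, eight of the nine settings are missed 79 to 95% of the time. A second design (correlation 0.6, control-only log-odds of 1 per SD, random drop-out in the intervention arm) gave 18%, 23% and 30% detection at about 10%, 19% and 28% drop-out.

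**Step 4: bias at T3 with independence GEE.** Bias = observed group difference − 0.72, in SD, with Monte Carlo standard error 0.010 to 0.012 over all trials.

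| Drop-out | Both arms, all trials | Control only, all trials | Control only, test not significant |
|---|---|---|---|
| 10% | -0.001 / -0.009 / -0.013 | -0.023 / -0.040 / -0.063 | -0.027 / -0.032 / -0.073 |
| 20% | -0.007 / -0.009 / -0.030 | -0.040 / -0.078 / -0.121 | -0.051 / -0.083 / -0.137 |
| 30% | -0.009 / -0.018 / -0.039 | -0.070 / -0.113 / -0.177 | -0.055 / -0.120 / -0.196 |

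The last two columns are about the same, so the gate does not screen out the biased trials.

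**Step 5: the working correlation.** In the second design, at about 11%, 22% and 31% drop-out, independence GEE was biased by -0.07, -0.11 and -0.18 SD. Exchangeable GEE on the same design gave 0.00, +0.01 and -0.01 SD.

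**Step 6: weighting without the gate.** With the true inverse-probability weights and a very large sample, bias under MAR drop-out was within 0.004 SD at 10 to 30% drop-out. Estimated weights at 70 subjects, and the mixed model proposed below, were not simulated.

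**The case against.** The plan does more than many: it states the assumption, names a check and a MAR alternative in advance, adopts intention-to-treat, and calls its effectiveness aims preliminary. Four stronger readings are tempting, and the article supports none of them.

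- **That the default analysis is biased.** This depends on the working correlation, which an article may leave to the full plan. With an exchangeable structure that fits, the bias in Step 5 disappears. That result rests on normal data whose true correlation matches the working one, so it is no general guarantee. The plan, which says GEE needs MCAR, does not appeal to it.
- **That the test usually misses non-MCAR drop-out whatever the mechanism.** Step 3 shows otherwise: strong dependence shared by both arms is found in 52% of trials at 10% drop-out and in 75 to 91% at 20 to 30%. Low power goes with weak or one-arm dependence.
- **That heavy drop-out is documented.** The Introduction reports that "more than 20% of the older participants stopped using the WMD during the 12-week intervention period". That concerns stopping the device in another study, not leaving this one. Questionnaire data here are collected by phone, so someone who stops wearing the device can still be followed. The planned figure is 10%.
- **That weighting cures informative drop-out.** If drop-out depends on unobserved values (missing not at random, MNAR), neither WGEE nor a mixed model removes the bias.

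Size also counts for the other side. At 10% drop-out the largest bias, about 0.07 SD, is roughly a quarter of the T3 standard error of about 0.26 SD. Any distortion of p-values from the two-step choice was not quantified, and nothing is claimed on it. These points limit the magnitude; they do not make a non-significant test evidence of MCAR.

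**Conclusion.** The decision rule is unsound as written and should be changed. Its likely effect at the planned drop-out is modest. With independence GEE and control-only dependence on the previous score, bias is about -0.02 to -0.07 SD at 10% drop-out (0.02/0.72 = 3% to 0.07/0.72 = 10% of the assumed effect). It reaches about -0.18 SD (25%) at 30%. When both arms share the mechanism it is at most about -0.04 SD up to 30% drop-out, and with a well-fitting exchangeable working correlation it is near zero. The sign means that the benefit is understated under this mechanism.

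The detection rates and biases rest on the simulation assumptions listed above, since the article gives neither a within-subject correlation nor a drop-out mechanism. The reading of the rule itself, and the point that non-rejection does not establish MCAR, need none of them.

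**What to change.** Remove Little's test as the gate and make a MAR-valid analysis primary whatever the test shows:

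- For continuous outcomes, preferably a likelihood-based mixed model for repeated measures, which needs no drop-out weights.
- For other outcomes, WGEE with a parsimonious drop-out model containing arm and previous outcome. With about 7 drop-outs there is no room for more covariates.
- Unweighted GEE, with its working correlation stated, as a sensitivity analysis.
- Little's test, if kept, as description only.

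This deals with MAR bias only. A sensitivity analysis for MNAR drop-out would have to be added separately.

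The cost is a change of wording and slightly more programming, with no effect on conduct or sample size. Standard errors may be slightly wider if the data really are MCAR, and WGEE weights may be unstable with so few drop-outs.
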